**Methods:**

**Aims:** The objective of this proposal is to undertake a pilot, feasibility RCT of a cell-based therapy for treatment of patients infected with SARS-CoV-2 virus related pneumonia to prevent progression to severe ARDS**.** The goal is to roll out an adequately powered, double-blind, randomised controlled trial after this pilot RCT.

**Hypothesis:** Expanded UCB derived cell therapy will be feasible, well tolerated and show potential efficacy in the treatment of acute COVID-19 related moderate to severe pneumonia as a result of their powerful anti-inflammatory and immunomodulatory properties.

**Collection and Expansion of UCB cells:** UCB is already being collected (from healthy pregnant volunteers at term gestation) and processed under strict TGA guidelines. The frozen UCB units will be sourced from Cell Care’s cord blood banks and released to our PC2 and certified grade D, ISO 9001 accredited Cell Therapy Platform Facility at the Monash Health Translation Precinct where they will be thawed, expanded using our expansion system and prepared for IV administration to eligible consented patients.

Once expanded, the cells will be fully tested, for microbes and cell viability, aliquoted and frozen using our GMP compliant, standard operating procedure (SOP) for cell expansion that is being developed. Prior to infusion, the requisite number of cells will be thawed and prepared for infusion. All SOPs for collection, processing, characterisation, storage, release, and preparation for infusion are currently in place for use of UCB cells for another current UCB trial that we are undertaking (CORD SaFe Trial, ACTRN12619001637134).

*Study design*

Pilot, safety and feasibility, randomised controlled trial.

*Blinding and Randomisation*

This will be an unblinded study, given that it is the first of its kind study (using expanded UCB cells) in COVID-19 patients. There will be no placebo infusion. Randomisation will be done by lead PI using computer generated allocation to intervention/ control groups (in blocks of 6 patients) by using sealed opaque envelopes prepared by an independent research nurse.

***P****opulation*

*Inclusion Criteria*:

Hospitalised patients with confirmed SARS-CoV2 infection (based on appropriate nucleic acid or other testing) meeting the following three criteria:

1. Expected to remain an in-patient for at least 48 hours,
2. Features consistent with viral pneumonia on Chest CT or X-Ray (in the opinion of the investigator), and

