3. Are unable to maintain a peripheral oxygen saturation of 95% or greater in room air

*Exclusion Criteria:*

1. Patients with known allergies to stem cell preparations.
2. Patients with known significant lung disease before COVID-19 presentation.
3. Patients receiving invasive/ mechanical ventilatory support.
4. Patients with underlying disease, comorbidities or clinical status that, in the opinion of the investigator, suggests death is imminent and/or likely to occur in the next 48 hours.
5. Patients currently on other investigational cell therapies.
6. Patients with known pregnancy.
7. Patient unable to provide consent.
8. The treating team deems that enrolment in the study is not in the best interests of the patient.

***I****ntervention group (n=12)*

Intravenous injection of expanded UCB cells at a dose of 5 million cells/kg. Maximum dose of 500 million expanded UCB cells. Standard supportive care will continue as needed.

The cell number/dosage should be easily achievable with the expansion technology that we have developed and reflects cell numbers currently being used in other COVID-19 MSC trials (12). Cell infusion will occur over 30-60 minutes through a peripheral intravenous cannula.

***C****omparison group (n=12)*

Standard supportive care will continue as needed*.*

***O****utcomes*

*Primary Outcomes:* Safety and tolerability of UCB cell administration (absence of immediate and short-term negative side effects); clinical improvement on a seven-category ordinal scale.

The seven-category ordinal scale consists of: 1, not hospitalised with resumption of normal activities; 2, not hospitalised, but unable to resume normal activities; 3, hospitalised, not requiring supplemental oxygen; 4, hospitalised, requiring supplemental oxygen; 5, hospitalised, requiring humidified nasal high-flow oxygen therapy, non-invasive mechanical ventilation, or both; 6, hospitalised, requiring invasive mechanical ventilation, ECMO or both; and 7, death. This ordinal scale has been used in previous Influenza and some COVID-19 trials (26, 27).

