*Secondary Outcomes:* Time to clinical stability (defined as the time from study randomisation until resolution of symptoms leading to discharge from hospital), individual symptom resolution, chest imaging changes (if available), need and duration of mechanical ventilation, incidence of secondary culture positive bacterial infections, and all-cause mortality (30- and 90- day). Immune response will also be studied using assay of inflammatory factors (IL-1b, IL-6, TNF-α and IL-10) from blood samples obtained prior to UCB cell infusion and at 1- and 7-days post infusion.

***T****imeframe*

6-12 months.

*Sample size and statistics*

As this is a pilot, feasibility RCT, a convenience sample size of 12 in each arm has been decided. Further, given the pilot nature of this RCT, significant efficacy is not expected, and hence only descriptive and interpretive statistics will be performed to compare groups as appropriate. This trial will help design an appropriately powered larger trial if treatment is well tolerated.

*Monitoring*

Regular vital monitoring for 24 hours post cell infusion will be conducted as detailed in the case report form.

Daily clinical evaluation of symptoms and classification according to the 7-category ordinal scale until one of the following time points: a) resolution of clinical symptoms b) death. In the hospital, this monitoring will be performed by review of the Electronic Medical Record and discussion with the treating team (unless an investigator is a member of the treating team and has direct contact with the patient). In the community, this will be performed by regular telephone contact. Follow up for other morbidities with 30- and 90-day telephonic contact will also be undertaken.

Routine blood tests, including full blood examination, C-Reactive Protein, liver and renal function, coagulation profile will be done as per treating clinical team directions.

Blood tests for immune response will be done before, and 24 hrs and 7 days after UCB cell infusion.

*Safety Reporting*

*Categorising safety related events:* Events will be categorised as per the National Health and Medical Research Council 2016 recommendation:

**Adverse event (AE)** Any untoward medical occurrence in a patient or clinical trial participant administered a medicinal/ biological product and that does not necessarily have a causal relationship with this treatment.

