**Adverse Reaction (AR)** Any untoward and unintended response to an investigational medicinal/ biological product related to any dose administered.

**Serious AE/AR (SAE/SAR)** Any adverse event/adverse reaction that results in death, is life-threatening, requires hospitalisation or prolongation of existing hospitalisation, results in persistent or significant disability or incapacity.

**Suspected Unexpected Serious Adverse Reaction (SUSAR)** An adverse reaction that is both serious and unexpected.

*Data Safety Monitoring Board (DSMB)*

An independent DSMB is being formed comprising of an intensivist, an infectious disease physician, and a scientist familiar with cell-based therapies to review all AE/ AR/ SAE/ SAR/ SUSARs and pre-decided reporting times (interim and final). Adverse incidents will be reported to the DSMB within 1 week of occurrence.

*Reporting to HREC*

The following reports will be submitted to HREC:

1. Any adverse event/ reaction deemed suitable by DSMB to temporarily halt the trial pending review.
2. An interim report after recruitment of 12 patients.
3. Any updates to protocol/ PICF.

*Data management*

Data will be collected prospectively by trial investigators and sourced from bedside clinical charts, monitors, electronic medical records and direct patient feedback. Data will be collected on a paper CRF and recorded in an electronic database. Paper records will be stored in a locked filing cabinet and electronic records will be kept on password protected documents. Data will be stored for 15 years.

*Ethics and oversight*

The clinical trial will be conducted in compliance with the protocol approved by Monash Health HREC and with the NHMRC National Statement on Ethical conduct in Human Research 2007 (updated May 2015). Fully informed, written consent will be obtained as per the participant information and consent form. Participation will be voluntary and option of withdrawal from trial will be possible at any stage. The trial will be overseen by investigator team members drawn from our ICU and infectious diseases teams, while the lead PI will have overall trial oversight and interaction with the DSMB and HREC.

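### Adverse events and early vital signs are anchored to the infusion, so the primary safety outcome has no stated concurrent control rate for them

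*Protocol*

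**What the plan says.** All references are to the Methods of the Protocol.

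- **Outcomes.** The first primary outcome is "Safety and tolerability of UCB cell administration (absence of immediate and short-term negative side effects". No between-arm form and no window are given.
- **Monitoring.** "Regular vital monitoring for 24 hours post cell infusion will be conducted as detailed in the case report form". No matching period is given for patients who are not infused.
- **Safety Reporting.** An adverse event is "Any untoward medical occurrence in a patient or clinical trial participant administered a medicinal/ biological product", with the qualifier that it "does not necessarily have a causal relationship with this treatment". An adverse reaction is a separate category: "Any untoward and unintended response to an investigational medicinal/ biological product related to any dose administered". Either becomes serious when, among other criteria, it "results in death, is life-threatening, requires hospitalisation or prolongation of existing hospitalisation".
- **Blinding and Randomisation.** The study is unblinded, and "There will be no placebo infusion". The comparison group has standard supportive care only.
- **Sample size and statistics.** "a convenience sample size of 12 in each arm has been decided". Groups are to be compared descriptively, and a larger trial is to be designed should the treatment prove well tolerated.

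Other follow-up is not tied to the infusion. Symptoms and the ordinal scale are assessed daily until resolution or death, and there are telephone contacts at 30 and 90 days for other morbidities. Mechanical ventilation, culture-positive secondary infection and 30- and 90-day mortality are secondary outcomes. Time to clinical stability is counted from randomisation.

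**The concern.** The participants have viral pneumonia and cannot hold 95% saturation on room air. Fever, desaturation, a longer stay and death can all arise from the illness. A randomised control arm is what shows how often they do. Here the two elements that feed the primary safety outcome most directly, the adverse event definition and the 24-hour vital-sign observation, start from receipt of the product. Patients who never receive it have no start point.

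Two things are at stake. First, the count of events in treated patients has nothing concurrent to be set against. Second, one arm is observed more closely than the other by staff who know the allocation, so a difference in recorded events could partly reflect a difference in looking. Tolerability is the stated condition for going on to a larger trial, so this outcome informs a real decision.

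**Working it through.** **1. The plan's own figure.** There is no calculation to reproduce. Twelve per arm is declared a convenience sample, and the protocol states no event rate, alpha, power or margin.

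**2. What is collected in which arm, as written.**

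| Item | Start point stated | Reaches controls? |
|---|---|---|
| 24-hour vital signs | Infusion | Not as stated |
| Adverse events | A product having been administered | Ambiguous |
| Adverse reactions | A dose of the investigational product | No, by nature |
| Serious events | Inherit the two rows above | Ambiguous |
| Daily symptoms and ordinal scale | Not tied to infusion | Yes |
| Ventilation, secondary infection, mortality | Not tied to infusion | Yes |
| 30- and 90-day morbidity contact | Not tied to infusion | Yes |

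The gap is therefore in adverse events that do not show in the lower three rows (fever, or desaturation too small to change the ordinal category) and in early vital signs. A common time zero was available, because time to clinical stability already runs from randomisation.

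**3. Why a treated-arm count alone is hard to read.** Inputs: n = 12 treated patients (Protocol, Sample size and statistics), and a background probability p that a patient has an untoward event from the illness alone. The protocol gives no p, so a range is assumed. With harmless cells and independent patients:

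P(at least one event among 12) = 1 − (1 − p)^12

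| Assumed p | (1 − p)^12 | P(at least one) | Expected patients with an event, 12p |
|---|---|---|---|
| 10% | 0.282 | 72% | 1.2 |
| 20% | 0.069 | 93% | 2.4 |
| 30% | 0.014 | 99% | 3.6 |

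At p = 5% the probability is already 46%. An observed 3/12 in the treated arm has an exact (Clopper–Pearson) 95% interval of 5.5% to 57%. Without a control count, such a result cannot be apportioned between illness and cells.

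**4. What a control count would add.** Suppose 3/12 in each arm, recorded in the same way. The Wilson 95% limits for 3/12 are 0.089 and 0.532. The Newcombe interval for the difference of 0 has half-width √[(0.250 − 0.089)² + (0.532 − 0.250)²] ≈ 0.325, so about −33 to +33 percentage points. For 6/12 against 3/12 the difference is +25 points, with 95% CI −12 to +54. A comparison becomes available, but a wide one.

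**The case against.** The strongest reply is that much of the harm data does reach controls. That stands. A reader might infer that safety is monitored only in infused patients and that the control arm gives no background rate at all. The Monitoring and Secondary Outcomes text does not support this: escalation of respiratory support, infection, later morbidity and death are followed without restriction by arm.

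A reader might also infer that illness events will be charged to the cells. The protocol does not say so. It separates adverse events, which need not be causal, from adverse reactions, and an independent DSMB reviews every category. Misattribution is a risk, since no rule for judging relatedness is stated, but it is not a stated consequence.

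Nor does the absence wording in the primary outcome amount to a rule that none of the 12 treated patients may have an event. No section sets such a criterion, so the probabilities above describe interpretability and not the chance of failing the trial.

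It is tempting to put a size on the ascertainment bias by assuming that some fraction of control events goes unrecorded. The documents give no capture rate, so any such figure would come wholly from the assumption.

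Three further points stand. The adverse event text speaks of a medicinal or biological product, whereas the adverse reaction text says an investigational one, so controls given other medicines may fall within the former. The wording is presented as a national recommendation; the weakness lies in applying it to an arm without an infusion and not extending it. And a 24-hour post-infusion check looks for infusion reactions, which have no true counterpart without a placebo infusion. The case report form, which holds the detail, is not shown.

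The reply does not dispose of the point. Who is observed, and from when, is a matter of data collection. An SAP cannot recover events that nobody recorded.

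**Conclusion.** The concern holds in a limited form. The adverse event definition and the early vital-sign monitoring are anchored to the infusion, and no equivalent time zero or window is stated for controls. Followed as written, the first primary outcome lacks a concurrent control rate for adverse events such as fever and for early vital-sign changes, and ascertainment differs by arm in an unblinded trial. The major harms do have control data.

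The size cannot be measured from the documents. The 72%, 93% and 99% rest on assumed background rates of 10%, 20% and 30% and on independence between patients; they show only that some events among the treated would be unsurprising with harmless cells. The conclusion also rests on the literal reading of an ambiguous adverse event definition and on a case report form that cannot be seen. If that form already collects the same items in both arms, what remains is a correction of wording.

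**What to change.** 1. In Safety Reporting, state that adverse events and serious adverse events are recorded for every randomised participant in both arms, over the same stated window from randomisation.
2. In Monitoring, state that the same 24-hour vital-sign items are abstracted from the routine chart for controls over a matched window, and define when that window starts.
3. In Outcomes, replace the absence wording with the number and proportion of patients with each class of event, by arm. List infusion reactions separately, because they have no control counterpart.
4. Align the case report form with these changes.

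The cost is protocol and form wording plus chart abstraction for 12 controls. They are expected to be in hospital for at least 48 hours under the first inclusion criterion, so routine charts should supply the data. No patients or procedures are added. The limitation to state openly is precision: at 12 against 12 the comparison remains descriptive, as the interval of about −33 to +33 points for 3/12 against 3/12 shows. The fix removes a difference in how events are found; it does not make the trial able to detect a modest excess of harm.

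### The primary ordinal outcome has no assessment day and its scoring stops at symptom resolution, so later changes in category are not collected

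*Protocol*

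**What the plan says.** Under Primary Outcomes (Protocol, Methods), the efficacy part of the primary outcome is "clinical improvement on a seven-category ordinal scale". No day and no size of improvement are attached to it. The favourable end of the scale reads "1, not hospitalised with resumption of normal activities", then "2, not hospitalised, but unable to resume normal activities", then "3, hospitalised, not requiring supplemental oxygen".

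The collection rule is under Monitoring: daily "classification according to the 7-category ordinal scale until one of the following time points: a) resolution of clinical symptoms b) death". No maximum day is given. After discharge the scoring goes on under the same rule: "In the community, this will be performed by regular telephone contact". The fixed-day contacts serve another purpose: "Follow up for other morbidities with 30- and 90-day telephonic contact will also be undertaken". The scale is not named there.

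Other measures do have days. Cytokines are taken before infusion and at days 1 and 7, and mortality is counted at 30 and 90 days. Time to clinical stability, a secondary outcome, runs from randomisation to the resolution of symptoms that leads to discharge. The study is unblinded, with 12 patients per arm and descriptive comparison only.

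**The concern.** The rule that ends scoring and the scale being scored measure different things. Scoring ends on symptoms, while categories 1, 2 and 3 are told apart by whether the patient is in hospital and has resumed normal activities. A symptom-free patient still in category 3 or 2 leaves the scoring before reaching the best category that he or she would have reached.

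Three further features add to this:

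- The stop depends on the outcome, so patients who resolve earliest lose scores earliest. If the arms differ in speed of recovery, they also differ in how many scores are missing on any given day.
- Resolution is judged without blinding, partly through discussion with the treating team, to which an investigator may belong.
- A patient who neither resolves nor dies has no stated end of scoring.

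At stake is the distribution of categories by arm on a common day. Sample size and statistics says that the pilot is to help design a larger powered trial, and this distribution is one of the natural inputs. An analysis plan could name a day or define improvement, but it could not supply scores that the protocol does not collect.

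**Working it through.** **1. No power figure to reproduce.** The sample is a convenience sample without alpha, power or effect size. The only arithmetic in the text, 12 + 12 = 24, agrees with the recruitment target.

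**2. Stop rule set against the scale.**

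| Category when symptoms resolve | Possible later change | Scored on the scale? |
|---|---|---|
| 3 (in hospital, no oxygen) | to 2 or 1, or worse | no |
| 2 (home, not back to normal activities) | to 1, or worse | no |
| 1 (home, normal activities) | worse only | no |

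**3. How many scores would have to be assumed on a fixed day.** The protocol gives no recovery or death rates, so these inputs are assumptions: 10% die in each arm, the rest resolve with exponential times of median m, and the day is d = 14. A death needs no assumed score, because it is 7. The share alive and already out of scoring is

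0.90 × (1 − 0.5^(d/m))

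| Assumed median m (days) | 1 − 0.5^(14/m) | Share with no day-14 score | Patients of 12 |
|---|---|---|---|
| 14 | 0.50 | 45% | 5.4 |
| 10 | 0.62 | 56% | 6.7 |
| 9 | 0.66 | 59% | 7.1 |
| 7 | 0.75 | 68% | 8.1 |

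With 14 days in one arm and 9 in the other, about 5 and 7 patients would need an assumed category. If 30%, 50% and 20% of them had stopped in categories 1, 2 and 3 (again assumed), 70% could still have improved: 0.70 × 5.4 = 3.8 and 0.70 × 7.1 = 5.0 patients. That 70% could in truth lie anywhere from none to all.

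**4. What the last recorded score would show.** A simulation of 200,000 patients per arm used Weibull resolution times (shape 1.5), a control median of 14 days and 10% deaths in each arm, falling uniformly over days 3 to 25. The 30/50/20 mix at resolution was the same in both arms. Patients not yet resolved were spread over categories 3 to 6 as 20/50/20/10. The measure is the probability that a treated patient scores better, with ties counted as half. The fixed-day columns carry the score at resolution forward.

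| Treated median (days) | Last score | Day 7 | Day 14 | Day 28 |
|---|---|---|---|---|
| 14 (no effect) | 0.50 | 0.50 | 0.50 | 0.50 |
| 10 | 0.50 | 0.55 | 0.57 | 0.54 |
| 7 | 0.50 | 0.62 | 0.65 | 0.55 |

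The last score stays at 0.50 even when recovery time is halved. This follows from the inputs: equal mortality and an equal mix at resolution leave nothing else for the last score to pick up. If either differed between arms, the last score would differ too.

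**5. Precision.** For 45% against 59% with 12 per arm, the standard error is √(0.45 × 0.55/12 + 0.59 × 0.41/12) = 0.20. A 95% interval is about ±40 percentage points around a 14-point difference.

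**The case against.** A reader might infer that the arms cannot be compared on recovery at all. The documents do not support that. Scores are daily up to the stop and go on by telephone after discharge while symptoms last, so time to a defined improvement can be derived. Time to clinical stability measures speed of recovery directly. Even the 45% against 59% above, read as the proportions alive and resolved by day 14, comes from data the rule already yields, because the day scoring stops is the day of resolution. What is missing is which of categories 1 to 3 those patients occupy on day 14.

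A reader might also infer that the plan compares last scores and so reduces to alive against dead. No section specifies a last-score comparison, and survivors can stop in category 1, 2 or 3, so such a comparison would not be binary. The choice of summary may properly sit in an analysis plan.

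Nor is relapse lost altogether. An adverse event that requires hospitalisation meets the definition of a serious event under Safety Reporting, and the 30- and 90-day calls cover other morbidities. It is only the ordinal score that is not taken again.

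The wording of time to clinical stability, which links symptom resolution to discharge, suggests that few patients may stay long in category 3 after resolution. That would narrow the gap between 3 and 2, but not the one between 2 and 1.

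Finally, this is a descriptive pilot with safety as the other primary outcome, and 12 patients per arm would estimate any distribution poorly. That stands, and it limits the weight of the point. It does not justify leaving the scores uncollected when one more assessment would supply them.

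**Conclusion.** The point holds in a limited form. The primary ordinal outcome has no assessment day. Its scoring ends at an outcome-dependent moment that is judged unblinded, and there is no last day for patients who neither resolve nor die. Changes in category after symptom resolution are not recorded on the scale. A fixed-day comparison would therefore rest on assumed scores at the favourable end, for roughly half of each arm on day 14 under the assumed rates (45% to 68% across medians of 14 to 7 days). A last-score comparison, if someone chose it, would not reflect speed of recovery. Time to improvement before the stop and time to clinical stability remain usable.

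The gap in collection follows from the text alone; its size depends on the assumed mortality, recovery times and mix of categories. The damage is to descriptive planning estimates that would be imprecise in any case, and no formal test is affected. The point merits correction before recruitment but does not stand in the way of the trial.

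**What to change.** Under Primary Outcomes, name one assessment day for the ordinal scale, for example day 14 or day 30. Count it from randomisation, since the control arm has no infusion to count from. Under Monitoring, keep daily scoring up to resolution as planned, and add that every randomised patient is scored on the named day whether or not symptoms have resolved, with death scored 7. Add the scale to the existing 30-day call. Present the distribution of categories by arm descriptively. With a named day, the primary outcome no longer depends on when scoring stops or on an open-ended follow-up.

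The cost is a line on the case report form and at most one extra call per patient, so no more than 24 calls. If day 30 is chosen, the existing call serves. Daily calls to day 30 are not needed, and a baseline-adjusted common odds ratio with 12 per arm is open to debate and not required for this correction.

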**Expected milestones and Key Performance Indicators:**

*Preparation for expansion of UCB cells* has already commenced and sufficient cells for first infusion will be ready by June 2020.

*Recruitment* of 24 patients to this pilot feasibility RCT, will be completed within 6-12 months of commencement.

*First participant* recruitment will commence in June 2020, subject to all SOPs being validated. We envisage recruitment of at least 4-6 patients, treatment and control, per month thereafter.

*Reporting* to our DSMB and HREC will be made at least twice (after recruitment of 12 patients and at completion), or following any adverse outcomes associated with the trial. Final report and preparation of manuscript for publication within 12 months of commencement of trial.

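### One reporting limit of up to a week to the DSMB covers every adverse event, fatal and life-threatening ones included, and the two accounts of HREC reporting do not agree

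*Protocol*

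**What the plan says.** Under Safety Reporting, the protocol defines AE, AR, SAE/SAR and SUSAR. The serious class covers "Any adverse event/adverse reaction that results in death, is life-threatening, requires hospitalisation or prolongation of existing hospitalisation", as well as lasting disability.

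Under Data Safety Monitoring Board, the board is "to review all AE/ AR/ SAE/ SAR/ SUSARs and pre-decided reporting times (interim and final"). The one time limit given there is "Adverse incidents will be reported to the DSMB within 1 week of occurrence". An adverse incident is not one of the defined classes, and no class has a different limit.

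Under Reporting to HREC, three items are listed. The first is "Any adverse event/ reaction deemed suitable by DSMB to temporarily halt the trial pending review". The second, which is periodic, is "An interim report after recruitment of 12 patients". The third covers changes to the protocol or the consent form.

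Under Expected milestones and Key Performance Indicators, the Reporting item states a minimum frequency: "to our DSMB and HREC will be made at least twice (after recruitment of 12 patients and at completion"). The same sentence then adds a trigger by event: "or following any adverse outcomes associated with the trial".

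**The concern.** Safety and tolerability form a primary outcome, and the protocol describes the study as the first to give expanded cord blood cells to COVID-19 patients. It classifies events by seriousness and expectedness, but the classes have no effect on how fast the DSMB is told. The DSMB can only decide on a halt after it has been told, and no interval between patients or pause during reporting is stated. Another patient could therefore be infused, in full compliance with the protocol, before the board hears of a death or a life-threatening reaction.

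The HREC text raises a second, separate problem. Staff working from the Methods list would send the committee only those events that the DSMB links to a halt. Staff working from the milestones would send any adverse outcome, plus a completion report.

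**Working it through.** The protocol states no figure on this point, so there is none to reproduce. The check has two parts.

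**1. Further infusions within the permitted week**

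Inputs:
- Reporting limit: 7 days from occurrence (Data Safety Monitoring Board).
- Allocation: 12 per arm, so half of recruits are infused (Intervention group; Comparison group).
- Accrual, first statement: "We envisage recruitment of at least 4-6 patients, treatment and control, per month thereafter" (Expected milestones).
- Accrual, second statement: 24 patients in 6 to 12 months (Expected milestones), that is 24/6 = 4 down to 24/12 = 2 a month. The first statement implies completion in 24/6 = 4 to 24/4 = 6 months. The two meet only at 4 a month, so the range 2 to 6 is used.

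Assumptions: Poisson arrivals, infusion soon after randomisation, recruitment still open, and a report made at the last permitted moment.

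Formulas: expected infusions λ = (monthly accrual / 2) × 7 / 30.44; P(at least one) = 1 − exp(−λ).

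| Recruits a month | Infusions a month | λ in 7 days | P(at least one) |
|---|---|---|---|
| 2 | 1 | 0.23 | 21% |
| 4 | 2 | 0.46 | 37% |
| 6 | 3 | 0.69 | 50% |

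With a 1-day window in place of 7 days, λ is 0.033, 0.066 and 0.099, and the probabilities fall to about 3%, 6% and 9%.

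**2. The two HREC texts side by side**

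| | Reporting to HREC (Methods) | Reporting (Expected milestones) |
|---|---|---|
| Which events | Those the DSMB judges fit for a temporary halt | Any adverse outcome associated with the trial |
| Report at 12 patients | Yes | Yes |
| Report at completion | Not listed | Yes |
| Time limit | None | None |

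On the Methods list alone, an event that does not prompt a halt has no event-specific route to the HREC. The next listed report is the interim one, due after 12/6 = 2 months, 12/4 = 3 months or 12/2 = 6 months of recruitment.

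**The case against.** The case on the other side corrects four stronger readings that a reader might infer.

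- *The DSMB will be told a week late.* The week is an upper limit, and a report on day 1 complies. The text supports only a delay of up to 7 days.
- *The DSMB is the only safeguard.* It is not. The protocol provides vital-sign monitoring for 24 hours after infusion, daily clinical evaluation, oversight by intensive-care and infectious-diseases investigators, and a lead investigator in contact with the DSMB and HREC. The study is unblinded, so allocation is known when an event occurs. The milestones also call for a report after any adverse outcome. What stands is that none of these carries a faster time limit or an obligation to pause.
- *A serious reaction that prompts no halt would never reach the HREC.* The 12-patient interim report could include it, and the milestones text supplies a direct route. Only the Methods list lacks one.
- *The two HREC rules cannot both be followed.* The Methods list is not worded as exclusive, so filing everything named in either place satisfies both. It is a failure to harmonise, not two incompatible duties.

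Two further objections stand in part. Earlier notification does not itself pause anything; it only lets the DSMB's judgement start sooner. And an expedited limit for every SAE, related or not, could load the DSMB with disease progression in patients hospitalised with COVID-19 pneumonia, so the short limit should be confined.

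The NHMRC 2016 recommendation does not visibly close the gap, since the protocol cites it for categorising events and not for time limits. An unseen SAP would not ordinarily set these limits either, and here the protocol has fixed one itself.

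**Conclusion.** The point holds in a limited form. As written, the protocol lets the DSMB learn of a fatal or life-threatening reaction up to 7 days after it happens, although the only described halt rests on that board's judgement. At 2 to 6 recruits a month, the chance of at least one further infusion before a report made at the limit is about 21% to 50%. That figure is conditional on an event having occurred and on the assumptions set out above. It would be lower if reports came earlier or investigators chose to wait, and it measures the chance of another infusion, not of harm. Even its low end matters with only 12 patients to be treated.

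The HREC texts differ on which events are reported and on the completion report. They are compatible if the broader one is followed, but the protocol does not say which governs. Both matters should be corrected before recruitment. Neither calls the design itself into question.

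**What to change.** 1. In the Data Safety Monitoring Board section, replace the undefined term for adverse incidents with the protocol's own classes and grade the limit by class. Give an expedited limit for serious events, for example 24 hours from awareness for SARs, SUSARs and fatal or life-threatening SAEs, and keep the existing week for the rest. The 24 hours is an illustration; the documents give no such figure.
2. Write one HREC rule and use it identically under Reporting to HREC and in the Reporting milestone. It should name the event classes to be reported, give a time limit, and include the completion report. Amending the Methods list alone to cover reactions and halts would still leave it narrower than the milestones text, so both places must change.

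The cost is protocol wording and a faster notification route. The downside is some additional expedited notices, because deterioration from COVID-19 often meets the SAE definition. Confining the short limit to suspected reactions and to fatal or life-threatening events keeps that small. The change concerns notification only and leaves treatment and the halt decision as they are.
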